## Abstract

**Background:** There is a great need for feasible interventions in the initial period after a trauma that minimize the risk of developing a clinically relevant PTSD. The majority of people suffer from severe sleep disorders after a traumatic event. Because sleep is essential for processing emotional memories, we aim to improve sleep quality in acutely traumatized patients to benefit adaptive trauma processing and thereby prevent PTSD development.

**Objective:** In a multicentre randomized controlled trial (RCT), we will investigate whether digital cognitive behavioural therapy for insomnia (dCBT-I) has the potential to not only increase sleep quality in acutely traumatized individuals but also reduce trauma-related symptoms (specific PTSD symptoms as well as related symptoms such as depression, anxiety and functional outcomes) and the risk for PTSD development in acutely traumatized individuals. Moreover, we will test if sleep disturbances pre-therapy predict the development of later PTSD symptoms.

**Method:** We aim to recruit 104 patients who will be randomly assigned to an app-based sleep intervention utilizing CBT-I or a sleep diary as an add-on to treatment-as-usual (TAU) in outpatient acute trauma centres. Sleep quality, PTSD symptoms and everyday functioning will be measured before, after the intervention and at a 6-month follow-up.

**Conclusion:** To our knowledge, this multicentre RCT is the first study to use dCBT-I as an early intervention for trauma. It may improve the understanding of the role of sleep in the development of PTSD and has the potential to contribute to the development of an easy-to-use early intervention for acutely traumatized individuals.

## Background

1.

### Post-traumatic stress disorder (PTSD) and the need for early interventions

1.1.

About 50–70% of adults worldwide experience at least one traumatic event in their lifetime, such as war events, physical or sexual violence, accidents or the unexpected death of a loved one. Such traumatic events can cause severe psychological difficulties. The majority of traumatized individuals remits spontaneously. Nevertheless, the conditional risk of PTSD, i.e. the prevalence of PTSD among those exposed to traumatic events ranges from 2.5% (Italy) to 17.6% (Northern Ireland) (Atwoli et al., 2015) with a subgroup of them experiencing the full symptoms of acute stress disorder before the manifestation of PTSD (Bryant et al., 2011). The core symptoms of PTSD encompass re-experiencing the traumatic event in the present (such as intrusions, flashbacks and nightmares), hyperarousal and avoidance of trauma reminders. PTSD and related disorders do not only cause significant distress and impairment of social and daily functioning but may even increase the risk of chronic physical illness (Scott et al., 2013). During the past decades, there has been an increasing effort to develop early psychological interventions aiming to prevent the onset of PTSD. According to the definition from the German guidelines for diagnostics and treatment of acute trauma, all interventions aiming at making the experience more apprehensible and reducing the risk of trauma sequela delivered within the first three months after trauma experience are referred to as early interventions (Bengel et al., 2019). These guidelines recommend early trauma-focused CBT (TF-CBT) for those who exhibit clinical symptoms of post-traumatic stress and active monitoring for those who display subclinical symptom burden (Bengel et al., 2019). However, trauma-focused early interventions are not accessible for the majority of traumatized individuals which increases the risk of manifestation of trauma-related symptoms. In search for feasible early interventions, researchers started to focus on the cognitive and emotional mechanisms that are known to be relevant in the context of PTSD development.

### The role of sleep in memory, emotion and PTSD

1.2.

PTSD can be conceptualized as a memory disorder in which the traumatic event is not properly consolidated and contextualized into autobiographical memory with some aspects of the traumatic event being easily re-experienced after sensory triggers and, oftentimes, amnesia for other parts of the traumatic event (Ehlers & Clark, 2000). According to a review by Colvonen et al. (2019), safety cues are not integrated in the traumatic memory and fear and arousal levels attached to the traumatic memory remain on a high level, leaving the traumatic memory poorly consolidated with incomplete emotional processing.

Healthy sleep enables memory consolidation and contextualization, mostly via transforming labile encoded memory traces into more stable permanent ones through reactivation of the memory during sleep (Rasch & Born, 2013). These memory functions of sleep are mostly related to slow-wave-sleep, more precisely to the coupling of slow oscillations, sleep-spindles and hippocampal ripples during that sleep stage (Born & Wilhelm, 2012). Another function of sleep that is also relevant to the processing of traumatic events is more closely associated with REM sleep. This sleep stage has been implicated in improving fear extinction and emotional processing by reducing the affective load attached to a freshly formed memory (Goldstein & Walker, 2014).

Sleep disturbances feature prominently in the diagnostic criteria for PTSD and Acute Stress Disorder (American Psychiatric Association, 2022). Up to 92% of patients with PTSD suffer from some form of sleep-related symptoms (Milanak et al., 2019). Especially nightmares and insomnia are often reported but restless leg syndrome, sleep apnea and fragmented REM sleep are also widespread (Colvonen et al., 2019) and many sleep disturbances share increased arousal as an underlying factor (Richards et al., 2020). Sleep disturbances are not only common after traumatic events and in PTSD, but pre-traumatic sleep problems and sleep reactivity (Reffi et al., 2023) are also considered a risk-factor for the development of PTSD (Pace-Schott et al., 2023). A spectral index derived from sleep EEG data even is discussed as a potential biomarker for PTSD since it has shown to distinguish patients diagnosed with PTSD from healthy controls with high effect size (de Boer et al., 2019). Both pre- and post-traumatic sleep disturbances might be involved in disturbed processes of fear extinction and emotional processing and a maladaptive consolidation of the traumatic event that are all characteristic of the development and maintenance of PTSD symptoms.

### The potential of sleep interventions for trauma processing

1.3.

As Bryant (2018) states in his review about current findings on of acute stress disorder, early interventions in the aftermath of a traumatic experience should influence key mechanisms that underpin acute traumatic stress. Targeting disturbed sleep in acutely traumatized individuals may provide such a mechanism by improving memory consolidation, emotional processing and fear extinction (Pace-Schott et al., 2023) which already have been identified as important targets for early trauma interventions (Bryant, 2021). Taken together, it can be assumed that sleep-related early interventions have the potential to reduce symptom load and potentially even prevent the development of PTSD (for a detailed discussion of this idea, see also Azza et al., 2020; Larson et al., 2023; Swift et al., 2022).

In our opinion, targeting insomnia symptoms in acutely traumatized individuals has the promise to the most direct route towards altering sleep architecture and spectral activity and thus influence the memory and emotion processing functions of sleep. There are pharmacological as well as psychotherapeutic approaches to target insomnia symptoms. Pharmacological treatment options such as sedative antidepressants, benzodiazepines, antipsychotics and melatonin are limited in applicability since they are either only recommended for short-term use due to risks and side effects, or there is a lack of evidence of their effectiveness (Riemann et al., 2017). Moreover, psychopharmacological agents alter sleep architecture. Benzodiazepines, for instance, decrease the deepest sleep stages as well as REM sleep (de Mendonça et al., 2023) which may hinder memory consolidation processes. Cognitive behavioural therapy for insomnia CBT-I is considered the gold standard and generally is strongly recommended as first-line treatment for chronic insomnia in adults of any age (Riemann et al., 2017).

CBT-I can be conceptualized alongside the cognitive model of insomnia by Morin (1993a) which states that insomnia symptoms are caused by an interaction of maladaptive sleep-related behaviours, cognitions and increased arousal. Accordingly, CBT-I typically includes sleep hygiene, and interventions to improve sleep efficiency such as stimulus control and bedtime restriction, elements of cognitive therapy targeting maladaptive sleep-related beliefs and cognitions as well as relaxation exercises (Harvey & Buysse, 2017). It is not only well established in the treatment of primary insomnia, but also shows considerable effects in comorbid insomnia (Geiger-Brown et al., 2015), including promising trials that used CBT-I as an add-on for the treatment of sleep disturbances in civilian as well as veteran samples meeting PTSD-diagnostic criteria (Colvonen et al., 2019; Talbot et al., 2014). There are also already a few promising studies which have not only examined the impact of CBT-I on sleep disturbances but also on PTSD symptoms in patients suffering from PTSD. Pigeon et al. (2022) reported a medium sized effect of CBT-I on PTSD symptoms. Moreover, in women with probable PTSD a recent study found a clinically relevant reduction of PTSD symptoms in the course of a 5-week manual-based CBT-I (Carlson et al., 2022). However, due to the lack of a control group in this study, it cannot be finally concluded that the reduction in symptoms is a consequence of the intervention and not of spontaneous remission. Gehrman et al. (2020) compared CBT-I delivered via tele-health to an in-person CBT-I program in persons diagnosed with PTSD and did find significant improvement in sleep quality which was comparable in both groups but no effect on PTSD symptoms. These interesting findings show the potential of CBT-I as an intervention for PTSD and raise the question of the effectiveness of CBT-I in acutely traumatized individuals, i.e. before a manifest PTSD has developed. Another advantage of CBT-I is that it can be administered in group interventions, individual therapy and has even become available in a digital format with comparable effects to in-person therapy (Lorenz et al., 2019). The latter also makes it a potentially economical and cost-effective intervention format.

### Research questions

1.4.

We therefore want to investigate whether a digital cognitive behavioural therapy for insomnia (dCBT-I) intervention delivered as an add-on to treatment as usual (TAU) can reduce trauma-related symptoms (specific PTSD symptoms as well as related symptoms such as depression, anxiety and functional outcomes) and the risk to develop PTSD in acutely traumatized individuals. Moreover, in an attempt to replicate previous findings, we will examine whether sleep disturbances pre therapy predict the development of later PTSD symptoms in this heterogeneous sample of acutely traumatized patients. More specifically, in line with previous studies we expect that measures of sleep continuity such as sleep efficiency and nightly awakenings will be especially indicative. They have lately been implicated in predicting PTSD symptoms in an EMA study (Schenker et al., 2023) and could indicate less deep, disturbed sleep and thus worse trauma memory processing (Kleim et al., 2016).

## Methods

2.

### Trial design

2.1.

The planned study is designed as a randomized between-subjects trial with two active groups (one intervention group receiving app-based CBT-I for approximately 8 weeks and one filling in a sleep diary for the same time span). The study intervention functions as an add-on intervention so both groups will receive TAU while undergoing study intervention. Therapists at the study centers delivering the TAU interventions will be blind towards study arm allocation of participants.

### Recruitment and setting

2.2.

Due to probable difficulties of accumulating a large enough sample size in only one center, recruitment is planned as a multicentre study in three outpatient clinics which use similar treatment approaches. To further increase similarity between centres, regular joint supervisions will be utilized. As currently planned, these supervisions will be held by an external supervisor every 6–8 weeks. In addition, we will organize one to two advanced training sessions per year. Therapists of the cooperating clinics will inform potentially eligible patients at the beginning of treatment in oral and written form about the study. If patients give written consent to be contacted by study conductors, clinics will provide patients’ contact data to study conductors. Study conductors will call the respective patients for a screening interview to ensure that all inclusion and exclusion criteria are met and decide on final inclusion in the study. A schematic overview of the whole study procedure is shown in Figure 1.

**Figure 1. F0001:**
[figure not shown]
Recruitment process of the study.

Cooperations are planned with trauma centers at the Departments of Psychiatry and Psychotherapy at the University of Luebeck as well as at the University Medical Center Hamburg-Eppendorf.

### Participants

2.3.

Participants aged between 18 and 55 years will be included in the study if they (1) have experienced a traumatic event within the past three months as measured with Life Events Checklist (LEC-5; Weathers et al., 2013) and show PTSD symptoms (PTSD Checklist for DSM-5 (PCL-5) score above cut-off value of 33) and (2) report on sleep disturbances which evolved or became stronger after the traumatic experience. Participants will be excluded from the study if they (1) take benzodiazepines or benzodiazepine receptor agonists, (2) report on a lifetime diagnosis of psychosis, bipolar disorder or more than two episodes of major depression, (3) have suffered from an alcohol or substance use disorder within the past year, (4) have an IQ < than 80 points, (5) are diagnosed with any systemic or neurological disorder (e.g. dementia), (6) show signs of acute suicidality, (7) are insufficiently able to communicate in German, (8) work in shifts or have had an intercontinental flight crossing two or more time zones within the past 30 days or (9) suffer from sleep apnea.

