### Randomization

2.5.

Participants will be equally (1:1) and randomly assigned to one of the two between-subjects conditions (intervention group receiving dCBT-I vs. control group filling in a sleep diary every day) while paying attention to matching both groups in age and gender. Study conductors cannot be blind due to practical reasons of study implementation.

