### Procedure and assessment

2.7.

After the recruitment procedure is completed, participants will provide written informed consent and are randomized to one of the two study conditions. Participants will then receive a link to an online questionnaire arranged in SoSciSurvey for baseline assessment (timepoint T0). Following baseline assessment, the intervention group will get access to the *somnio* app and receive dCBT-I for the subsequent 8 weeks whereas the control group will fill in an online sleep diary every day (link provided by email). Five weeks after the start of the intervention, participants will receive a phone call to encourage compliance and spot potential issues with the use of the app or sleep diary. Both groups will continue to participate in TAU of the respective clinic without any limitations. After the intervention phase (10 weeks post baseline), all participants will receive a link to a second online assessment (timepoint T1). Additionally, the researchers conducting the study will contact every participant for a phone interview around T1 to gather information about current medication, number, and content of trauma-related outpatient treatment sessions. Six months after baseline assessment, participants will be contacted again and asked to fill in a follow-up assessment (T2). All measures used for the assessments on different time points are listed in Table 2. At all assessments, participants have the possibility to pause filling out the questionnaires in case they become overwhelmed and are allowed to resume at a later point during assessment day.

**Table 2. T0002:** Measures used for the assessments on different time points.

	Pre-intervention	Post-intervention	
	T0	T1	T2
Demographic data	x		
Sleep diary	x	x	x
MCTQ	x		
PSQI	x	x	x
LEC-5	x		
PCL-5	x	x	x
PCTI	x	x	x
CTQ	x		
BDI-II	x	x	x
BAI	x	x	x
WHODAS 2.0	x	x	x

Abbreviations: *BAI*, Beck Anxiety Inventory; *BDI-II*, Beck-Depressions-Inventar; *CTQ*, Child Trauma Questionnaire; *LEC-5*, Life Events Checklist for DSM-5; *MCTQ*, Munich ChronoType Questionnaire; *PCL-5*, PTSD Checklist for DSM-5; *PCTI*, Post-traumatic Cognitions Inventory; *PSQI*, Pittsburgh Sleep Quality Index; *WHODAS 2.0*, WHO Disability Assessment Schedule.

x, Instrument is assessed at respective timepoint.

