#### Primary outcome measures

2.8.1.

The primary outcome measures are PTSD symptom severity and number of participants with probable PTSD according to a PCL-5 cut-off of 33, which showed the best sensitivity-to-specificity-ratio for detecting PTSD (Weathers et al., 2013). Due to the online-design, we could not use CAPS interview as Pigeon et al. (2022) did to survey PTSD symptom development and decided to use PTSD Checklist for DSM-5 (PCL-5; Weathers et al., 2013) and Post-traumatic Cognitions Inventory (PCTI; Foa et al., 1999) as self-reports instead, both applied at T0, T1 and T2. Whereas the PCL-5 covers all PTSD symptoms, PTCI specifically measures trauma-related cognitions. The PCL-5 asks respondents to rate bothering of PTSD symptoms during the past month on a 5-point likert scale (1 = not at all to 5 = extremely) and has strong internal consistency (*α* = .94), test–retest reliability (*r* = .82), and convergent (*rs* = .74 to .85) and discriminant (*rs* = .31 to .60) validity (Blevins et al., 2015). The PTCI consists of 33 questions about trauma-related cognitions (based on the three factors Negative Cognitions About Self, Negative Cognitions About the World and Self-blame) which respondents rate on a 7-point-likert scale (absolutely no consent to strong consent). As PCL-5, PTCI shows excellent psychometric properties with internal consistency ranging from *α* = of .86–.97 (Foa et al., 1999). As the PCL-5 contains the item ‘Trouble falling or staying asleep?’ (Weathers et al., 2013), all analyses for the PCL-5 will be conducted with and without this item separately to detect whether potential changes on this measurement are solely driven by changes in sleep quality.

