### Statistical analysis

2.9.

Statistical analyses will be based on a mixed general linear model design with the two-level between group factor intervention (intervention vs. control group) and the three-level within group factor time (assessments at T0, T1 and T2) for primary and secondary outcome measures to account for both hypotheses tested in this study. A multilevel approach including study centers with their, presumably, differing TAU interventions, is not feasible due to too low a number of study centers at this hierarchical level. However, as discussed below, study centre and TAU interventions will be used as covariates and for exploratory analyses. For the first research question, the interaction between groups and time will be analysed to determine whether PTSD symptom severity differs for the intervention group after receiving the add-on treatment. For the second research questions, sleep disturbance before the intervention will be used to predict PTSD symptom severity at first and second follow-up for both groups. Due to the exploratory nature of this study, analysis will be conducted both with an intention-to-treat and a per-protocol approach, allowing for a comparison of both effect estimates (Gupta, 2011). For intention-to-treat analysis, dropouts will be included with a last observation carried forward strategy. Extreme cases and outliers will be checked for validity and excluded for per-protocol analysis if indicated. Dropouts will be reported with time point and reason in the final results. We intend to include age, gender, severity of trauma (indicated by classification in type-1 and -2 traumata), number of previous traumatic events, content of trauma-related outpatient treatment sessions and recruiting centre as covariates and in further exploratory analyses. Despite our efforts to proactively reduce variance in trauma treatment among participating trauma centers by organizing joint supervisions, we assume there will be left some significant variance that has to be considered in the statistical analyses. The content of trauma-related outpatient treatment sessions will be classified into trauma-focused versus non-trauma-focused therapy elements since it has been shown that in symptomatic acutely traumatized individuals this may cause a significant difference in treatment outcome (Roberts et al., 2019). Furthermore, we will survey whether sleep interventions have been included in the therapy process or not. By this, we intend to control for the most relevant confounding factors arising from between-participant-treatment-differences.

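### Time since trauma varies from zero to three months at entry but is neither a matching factor nor a named covariate; this costs some precision in the randomized comparison and may confound the sleep-prediction question

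*Protocol article*

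**What the plan says.** Section 2.3 requires that participants "have experienced a traumatic event within the past three months as measured with Life Events Checklist" and score above 33 on the PCL-5. It sets an upper limit on the interval since the event and no lower one.

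The follow-up clock starts at baseline. Section 2.7 places T1 ten weeks after baseline, and for T2 it says "Six months after baseline assessment, participants will be contacted again".

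Section 2.5 assigns participants 1:1 "while paying attention to matching both groups in age and gender". No other balancing factor is named.

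Section 2.9 lists the covariates: "We intend to include age, gender, severity of trauma (indicated by classification in type-1 and -2 traumata), number of previous traumatic events", followed by "content of trauma-related outpatient treatment sessions and recruiting centre as covariates and in further exploratory analyses". That makes six: age, gender, trauma type, number of previous traumas, content of treatment as usual, and centre. Time since the index event is not among them, and Table 2 does not show it as a separate item.

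The first research question is tested by the group-by-time interaction. For the second, "sleep disturbance before the intervention will be used to predict PTSD symptom severity at first and second follow-up for both groups".

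Two further statements bear on timing. Section 1.1 says "The majority of traumatized individuals remits spontaneously". Section 2.8.1 says "The PCL-5 asks respondents to rate bothering of PTSD symptoms during the past month".

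**The concern.** The article treats timing as important. Its Discussion rests the rationale on intervening before maladaptive processing has become manifest, and section 1.3 faults an uncontrolled study because its improvement might be spontaneous remission. Yet the analysis model has no term for where each person stands on the course after trauma.

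Someone enrolled soon after the event may have more natural recovery ahead than someone who still scores above the cut-off close to three months. With visits tied to baseline, the two are compared at different distances from the event. For anyone enrolled within a month of the event, the one-month PCL-5 recall period at T0 also reaches back before it.

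Two things are at stake:

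- **First question (randomized).** If timing predicts change in PCL-5, that variation stays in the error term, and the arms may differ in mean timing by chance.
- **Second question (not randomized).** Timing may relate both to sleep at T0 and to later PTSD severity. Section 1.4 gives the predicted association a mechanistic reading, from disturbed sleep to poorer trauma-memory processing. A shared dependence on timing would weaken that reading.

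**Working it through.** **Inputs from the article:** entry 0 to 3 months after trauma (2.3); T1 at 10 weeks and T2 at six months after baseline (2.7); Cohen's f = 0.25, power 80%, alpha 5%, required N = 86 (2.4); two arms, 1:1 (2.5); three assessments (2.9).

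**Assumptions, not in the article:** correlation of 0.5 between assessments; entry times uniform over 13 weeks; every figure for the effect of time since trauma.

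1. **The plan's own N.** For a between-factor effect in a mixed design, λ = f²·N·m / (1 + (m − 1)ρ) = 0.0625 × 86 × 3 / (1 + 2 × 0.5) = 8.06, with 1 and 84 degrees of freedom. Power is 0.801; at N = 84 it is 0.792. N = 86 is reproduced.

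2. **Spread of timing at the visits.** T1: 10 + 0 to 10 + 13 = 10 to 23 weeks after trauma. T2: 26 + 0 to 26 + 13 = 26 to 39 weeks.

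3. **Chance imbalance between arms.** SD of a uniform distribution over 13 weeks = 13/√12 = 3.75 weeks. With 43 per arm, SE of the difference in means = 3.75 × √(2/43) = 0.81 weeks, and 1.96 × 0.81 = 1.6 weeks. If entry is instead uniform over weeks 3 to 13, the SD is 10/√12 = 2.89, the SE is 0.62, and the 95% range is about ±1.2 weeks.

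4. **What that imbalance could move.** If change differs by 0.5 to 1 PCL-5 point per week of delay (assumption), a 1.6-week imbalance shifts the contrast by 0.8 to 1.6 points.

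5. **Precision.** If time since trauma explains a share R² of outcome variance, the adjusted effect size is f/√(1 − R²). On the plan's between-factor calculation:

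| R² (assumed) | Power at N = 86 | Required N |
|---|---|---|
| 0 | 0.801 | 86 |
| 0.02 | 0.809 | 86 |
| 0.05 | 0.821 | 82 |
| 0.10 | 0.841 | 78 |
| 0.15 | 0.861 | 74 |
| 0.20 | 0.881 | 70 |

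   The slopes in step 4 point to the lower rows. With an outcome SD of 15 points (assumption), they imply r = 0.5 × 3.75/15 = 0.125 to 1 × 3.75/15 = 0.25, so R² = 1.6% to 6.3%. Then 86 adjusted participants are worth 86/0.984 ≈ 87 to 86/0.9375 ≈ 92 unadjusted ones.

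6. **Sleep prediction.** Leaving out time since trauma shifts the standardized sleep coefficient by r(sleep, time) × β(time). With |r| from 0.1 to 0.3 and β from 0.1 to 0.3 (assumptions), the shift runs from 0.1 × 0.1 = 0.01 to 0.3 × 0.3 = 0.09 in absolute value. Its sign follows the sign of r, which the article does not give.

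7. **Where the covariate must enter.** The first question is tested by group × time. A baseline covariate entered only as a main effect moves a person's level equally at T0, T1 and T2, so it does not model recovery that differs by entry time. That needs a covariate × time term.

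**The case against.** A reader might infer that natural recovery biases the treatment comparison. It does not. Allocation is random with a concurrent control arm, so recovery affects both arms equally in expectation. The imbalance in step 3 is ordinary chance variation that the test's error rate already allows for. T0 is a level of the time factor, so stable differences between people do not enter the interaction test. What remains is efficiency.

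A reader might also take section 1.1 to mean that the trial's participants mostly remit. That sentence concerns traumatized individuals in general. Entrants score above 33 on the PCL-5, report sleep disturbance that began or worsened after the event, and are starting clinic treatment. The article gives no remission rate for them, so it does not show that timing is a large source of variance.

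The spread may be narrower than zero to 13 weeks, because clinic intake, consent to contact, telephone screening and randomization all precede T0. This stands, and step 3 shows its effect.

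For the sleep question, neither the size nor the direction of any distortion is known, and the study calls itself exploratory. This stands too, but it favours prespecifying the term over choosing it after seeing the data.

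Finally, model details may belong in an analysis plan that is not shown, and the covariate sentence states an intention. But section 2.9 names six covariates individually. It makes a selection, and timing is not in it.

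**Conclusion.** The point holds as a modest gap in the covariate plan. The omission is a stated choice: sections 2.5 and 2.9 name their factors, and time since trauma is in neither.

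Its weight falls mainly on the second research question, where randomization gives no protection. There, time since trauma is a plausible confounder of unknown size and direction; the 0.01 to 0.09 shift rests wholly on assumed correlations. For the first question the consequence is possible lost precision and chance imbalance of about ±1.6 weeks at 43 per arm, or about ±1.2 weeks if nobody enters before week 3. The gain in power from adjusting also depends on an assumed R², and is slight if that is only a few per cent.

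The article does not support the stronger conclusions that the treatment effect is biased, that the sleep association is distorted in a particular direction, or that N = 86 is wrong.

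**What to change.** In section 2.9:

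- Add time from index event to T0, continuous in weeks, as a prespecified baseline covariate.
- In the PCL-5 group × time model, enter it together with its interaction with assessment time.
- In the sleep-prediction model, enter it as a covariate.
- Label any split at one month after trauma as descriptive; the sample is sized only for the overall effect.

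In section 2.7 and Table 2, state that the index-event date is recorded at T0. Its approximate timing must already be established to apply the first entry criterion, so the burden is small.

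The cost is one degree of freedom for the main effect and two for the interaction across three assessments in the PCL-5 model, and one in the sleep-prediction model. Entry criteria and N = 86 need no change. The covariate does not repair the recall overlap at T0 for people enrolled within a month of the event; that should be acknowledged when baseline scores are interpreted.

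### Everyone enrolled already meets the trial's own definition of probable PTSD at screening, so the binary primary outcome measures persistence or remission, not the development of PTSD

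*Protocol article*

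**What the plan says.** **Entry.** Section 2.3 requires that participants "have experienced a traumatic event within the past three months" and "show PTSD symptoms (PTSD Checklist for DSM-5 (PCL-5) score above cut-off value of 33". Section 2.2 has the criteria checked in a telephone screening call before final inclusion. Section 2.7 puts consent and randomization next, and only then the online T0 questionnaire.

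**Outcome.** Section 2.8.1 names two primary outcomes: PTSD symptom severity and the "number of participants with probable PTSD according to a PCL-5 cut-off of 33". It justifies the value as the one "which showed the best sensitivity-to-specificity-ratio for detecting PTSD". The same section says that the CAPS interview could not be used.

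**Aim.** The Abstract wants to reduce "the risk for PTSD development in acutely traumatized individuals"; section 1.4 repeats this as "the risk to develop PTSD in acutely traumatized individuals". Section 1.3 places the intervention "before a manifest PTSD has developed". Section 3 names prevention as a possible benefit.

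**Item coding.** Section 2.8.1 describes the PCL-5 response format as a "5-point likert scale (1 = not at all to 5 = extremely".

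**The concern.** A trial can show a lower risk of developing a condition only in people who do not yet have it by the definition in use. Here the rule that admits people is also the rule that counts them as cases. If the intervention arm has fewer people above 33 at T1 or T2, the correct reading is that more of them remitted. Under the aims as worded, the same result would be reported as a reduced risk of developing PTSD. That is a different claim, with different consequences for who should be offered the intervention.

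**Working it through.** **1. The plan's own figure.** Section 2.4 gives N = 86 for f = .25, 5% type I error and 80% power, for a between-factor effect in a mixed design. With 2 groups, m = 3 assessments and a correlation of ρ = 0.5 between them (assumed; the article states none), the noncentrality is λ = f²·N·m / (1 + (m − 1)ρ) = 0.0625 × 86 × 3 / 2 = 8.06 on 1 and 84 degrees of freedom. Power is 0.801; N = 84 gives 0.792. So 86 is reproduced. It rests on the continuous effect size, and nothing below changes it.

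**2. Entry rule against outcome rule.** Assume whole-number totals.
- Entry: PCL-5 above 33, so at least 34.
- Outcome: cut-off of 33. The article does not say whether 33 itself counts, but a score of 34 or more is a case under either reading.
- Result at screening: 104 of 104 (100%) are cases; 104 − 104 = 0 are non-cases.

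**3. Does anything else separate a case at entry from a case at T2?**
- Exclusions: none of the nine in section 2.3 concerns existing PTSD.
- Duration: the outcome has no duration criterion, and the PCL-5 covers the past month at every administration.
- Diagnosis: no diagnostic interview is used.
- Time since trauma: up to three months, with no minimum.

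By the trial's measure, the two states are identical.

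**4. What the outcome can record.** Above the cut-off at screening and at T1 or T2 is persistence. Above at screening and below later is remission. Someone who dips below at T0 and is above again later has returned to case status; that is not a first onset.

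**5. How many may be below 33 at T0.** T0 is a later, separate administration with no PCL-5 requirement. Take screening and T0 scores as bivariate normal, with the retest correlation of .82 from section 2.8.1 and, as assumptions, a mean of 35 to 50 and an SD of 12 to 15 before selection. Simulating Pr(T0 < 33 | screening > 33):

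| Mean | SD 12 | SD 15 |
|---|---|---|
| 35 | 16.9% | 17.4% |
| 40 | 11.3% | 12.8% |
| 45 | 6.9% | 8.8% |
| 50 | 3.7% | 5.7% |

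Of 104 people this is about 4 (0.037 × 104 = 3.8) to 18 (0.174 × 104 = 18.1). All of them were cases at screening.

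**6. What the outcome can still show, read as persistence.** This is an illustration only, since the article gives no persistence rate. With n = 43 per arm (86 / 2) and a two-sided 5% test, power = Φ{[(p₁ − p₂) − 1.96·√(2p̄(1 − p̄)/n)] / √([p₁(1 − p₁) + p₂(1 − p₂)]/n)}. For 60% against 30%: (0.30 − 1.96 × 0.1073) / 0.1023 = 0.88, so power is 0.81. At 80% power, the contrasts for other assumed control rates are 80% against 51.5%, 50% against 21% and 40% against 13.5%. The comparison is meaningful, but as remission.

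**7. Item coding.** With k items, coding from 1 instead of 0 adds k to every total, so 33 marks a different symptom level under each coding. The article gives neither k nor the coding for which 33 was derived, so the shift cannot be sized from it.

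**The case against.** The best defence is that a high score soon after trauma is acute stress, not established PTSD. Section 1.1 defines early intervention as falling within three months of the trauma, says that most people remit without treatment, and describes acute stress disorder as preceding PTSD in some. Section 2.3 speaks of symptoms, not of a diagnosis. On this view the authors want to stop early symptoms from persisting. That is a sensible aim, and the three-month window is not in itself a flaw. But the outcome as defined does not carry the distinction, and persistence is the word that the aims lack.

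It can also be said that section 2.9 rests on the group-by-time interaction for symptom severity, that section 3 gives the purpose as reducing sleep disturbance and trauma-related symptoms and hedges its prevention wording, and that the study is called exploratory. All of this is true, and it limits the damage. It does not cover the Abstract and section 1.4, where reduced risk of development is a stated objective.

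Several stronger readings are tempting, and the article does not support them:
- *Everyone is a case at T0, so status can only move from case to non-case.* The criterion is met at screening; T0 comes after randomization, and some may score below 33 there.
- *Regression to the mean after selection above 33 biases the result.* It acts in both randomized arms and does not bias the contrast between them.
- *The cut-off of 33 is wrongly kept for the score without the sleep item.* Section 2.8.1 says only that analyses are run with and without that item; it names no cut-off for the shortened score.
- *The 1-to-5 coding shows that 33 is the wrong value.* The article lacks the figures needed to say so.

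**Conclusion.** The point holds as a mismatch between the binary primary outcome and the stated aim. At screening, 100% of participants meet the trial's case definition and 0 of 104 are at risk of a first case by that definition. This follows from the article's own text and needs only the assumption of whole-number scores. The proportion above the cut-off at T1 or T2 is therefore a measure of persistence or remission. It cannot support a reduced risk of developing PTSD, nor a conclusion of prevention.

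A reader might infer that the trial is invalid or wrongly sized. It is not, on this ground: the between-arm comparison, the continuous PCL-5 outcome and the N = 86 calculation are untouched. The coding question is a separate, minor request for confirmation and adds no weight to the main point.

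**What to change.** 1. In section 2.8.1, define the binary primary outcome as persistence (or, equivalently, remission) of probable PTSD at T1 and T2 among people above the cut-off at screening. That is everyone randomized, so the intention-to-treat set is kept. State whether a score of exactly 33 counts as a case.
2. Reword the aims in the Abstract and section 1.4, and the prevention statements in sections 3 and 4 where they describe what this trial may show, as persistence or remission.
3. Confirm that the item coding used for scoring is the one to which 33 applies, for eligibility and outcome alike.

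The cost is wording and a less ambitious claim; no patients, visits or measures are added. The change should be made before results by arm are known, so that it is not a later redefinition of a primary outcome. If onset is truly the target, it needs a criterion that participants do not already meet at entry, which would be a change of design.
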